#### Exploratory outcomes

2.7.4

To explore the potential mechanisms by which CJG may treat pGGNs, a longitudinal biospecimen collection protocol has been established. Paired saliva and feces samples will be collected at baseline, mid-term (months 1 and 2), and end (month 3) of CJG treatment. For saliva, participants will fast for 2 h, rinsed their mouths, and collected 2–3 mL of unstimulated saliva by drooling into a sterile tube, which will then be frozen on dry ice and stored at −80° C. For feces, participants will collect approximately 5 g at home using sterile tools, avoiding air exposure and toilet water. These samples will be initially kept at −20° C and later transferred on ice to a central lab for storage at −80° C.

After assessing sample quality, total genomic DNA from microbial communities will be extracted. The V3-V4 regions of 16S rRNA will be amplified for high-throughput sequencing. Sequences will be preprocessed through filtering, denoising, and chimera removal, resulting in amplicon sequence variants (ASVs) for bioinformatic investigations. This will include *α*-diversity analysis with Shannon and Chao1 indices, *β*-diversity exploration using principal coordinate analysis (PCoA) with Bray-Curtis distance, genus-level species differentiation via Linear discriminant analysis Effect Size (LEfSe), and examining the relationship between microbial genus abundance and time using multivariate linear association (MaAsLin).

Metabolites were extracted from saliva and feces using a chilled methanol–water solution. After centrifugation, the supernatant was analyzed by LC–MS. The raw data were processed for peak alignment, de-noising, and normalization. Multivariate statistical analyses, such as principal component analysis (PCA), partial least squares discriminant analysis (PLS-DA) and orthogonal PLS-DA (OPLS-DA), identified differential metabolites (VIP > 1 and *p* < 0.05). Kyoto encyclopedia of genes and genomes (KEGG) enrichment analysis revealed altered pathways. The Benjamini-Hochberg method was used to calculate the false-discovery rate (FDR) for multiple comparisons, with significance set at *P*_FDR_ < 0.05.

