The direct cellular impacts of the human microbiota and microbial metabolites have the potential to reprogram the pulmonary microenvironment, thereby facilitating early-stage lung cancer. Current research suggests that the lung microbiome *Faecalibacterium* and *Blauti*a may exert protective effects against the progression of early lung cancer from ground-glass nodules to solid nodules, whereas *Ralstonia* may contribute to malignant transformation (30). The metabolites of these microbes are primarily involved in energy metabolism pathways. Additionally, the microbiota plays a crucial role in the translation of TCM. TCM extracts, monomers, and compound formulations can exhibit antitumor effects by modulating the composition of the gut microbiota and endogenous metabolites, restoring the integrity of the intestinal barrier, and regulating immune and metabolic processes (31). Our team developed a lung nodule risk prediction system using 16S rRNA sequencing and machine learning, which identified distinct salivary microbiota profiles between persistent nodules and healthy controls, as well as between benign and malignant nodules (32, 33). Besides, our up-front clinical trial on gut microbiota during CJG intervention for ground-glass nodules in the lung showed that this formulation altered gut microbiota, notably increasing *Weissella* abundance, which may influence clinical outcomes (34). However, this study specifically includes ground-glass nodules patients combined with constipation. And the small sample size, short duration, and unstable microbial findings limited deeper exploration of the interactions between CJG, gut microbiota, and ground-glass nodules. Thus, we hypothesize that CJG may affect pGGNs by altering the oral and gut microbiota’s composition and metabolic pathways. Our integrated multi-omics approach (16S rRNA sequencing and GC–MS metabolomics) serves as a powerful *in vivo* “wet lab” experiment conducted directly on patient-derived biospecimens. By analyzing the salivary and gut microbiota alongside their metabolic profiles, we aim to move beyond correlation and infer potential causal biological pathways through which CJG may exert its effects. Subsequent KEGG pathway enrichment analysis of identified differential metabolites will specifically highlight altered host or microbial metabolic pathways (e.g., involving inflammation, oxidative stress, or cellular proliferation), effectively bridging the gap between CT imaging findings and underlying molecular mechanisms. This bioinformatic exploration provides a robust hypothesis-generating framework for future targeted *in vitro* or *in vivo* mechanistic studies on specific signaling pathways.

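### The steps listed for the mechanism analysis never use a nodule outcome, so they cannot support the Discussion's claim to go beyond correlation and link CT findings to molecular pathways

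*Protocol article*

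**What the plan says.** Section 2.7.4 (Exploratory outcomes) opens with its purpose: "To explore the potential mechanisms by which CJG may treat pGGNs, a longitudinal biospecimen collection protocol has been established". It then lists the analysis.

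- Microbiome: Shannon and Chao1 indices, PCoA on Bray-Curtis distance, LEfSe at genus level, and "examining the relationship between microbial genus abundance and time using multivariate linear association (MaAsLin").
- Metabolites: PCA, then "partial least squares discriminant analysis (PLS-DA) and orthogonal PLS-DA (OPLS-DA), identified differential metabolites" at VIP > 1 and p < 0.05. After that, KEGG "enrichment analysis revealed altered pathways", with Benjamini-Hochberg control at FDR < 0.05.

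Section 2.14 models change in nodule diameter on group, time, their interaction, age and baseline diameter.

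The Discussion says what the omics work is meant to deliver: "we aim to move beyond correlation and infer potential causal biological pathways through which CJG may exert its effects". It continues: "Subsequent KEGG pathway enrichment analysis of identified differential metabolites will specifically highlight altered host or microbial metabolic pathways", and describes this step as "effectively bridging the gap between CT imaging findings and underlying molecular mechanisms". The same paragraph ends by calling the exploration a hypothesis-generating framework for later laboratory studies.

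Saliva and stool are collected at baseline and months 1, 2 and 3 (section 2.7.4). CT is measured at baseline, 3 months and 1 year (section 2.7.1).

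**The concern.** A statement about how CJG acts on nodules needs some analysis in which the nodule appears. The listed steps contain none, not even a simple correlation between a feature and nodule change. Yet the Discussion says the work goes further than correlation, and attaches the link to CT to KEGG enrichment, a step whose only input is a list of metabolites.

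Exploring the mechanism is a stated aim in the Abstract and Introduction. Two situations matter. CJG may change saliva or stool chemistry and leave nodules alone, or it may shrink nodules by a route unrelated to the pathways found. In either case the listed steps would yield the same kind of pathway list, which the Discussion's wording invites the reader to take as an explanation of the CT result. The trial collects the data needed to examine the difference, but no stated step uses them for that.

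**Working it through.** **1. Inputs of each stated step**

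| Step | Inputs | Nodule variable? |
|---|---|---|
| Shannon, Chao1, PCoA, LEfSe | genus or ASV abundances, a class label | no |
| MaAsLin | genus abundance, time | no |
| PCA, PLS-DA, OPLS-DA, p-value, FDR | metabolite levels, a class label | no |
| KEGG enrichment | list of differential metabolites | no |
| Mixed model for diameter (2.14) | group, time, age, baseline diameter, diameter change | yes, but no omics term |

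**2. What follows.** Write X for the omics data, L for the label (arm or time) and Y for nodule change. The rule that names a pathway is a function of X and L only. Its probability of naming a pathway depends on the distribution of X given L and not on Y. Hold CJG's effect on X fixed, and that probability is the same for every possible effect on Y. This is true by construction; the simulation below only gives it a scale.

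**3. Number per arm.** Section 2.9 gives changes of 1.11 (SD 2.12) and 0.19 (SD 1.25) mm, two-sided α 0.05, power 0.90 and 10% dropout. The difference is 1.11 − 0.19 = 0.92 mm. The variance sum is 2.12² + 1.25² = 4.494 + 1.563 = 6.057. The normal approximation gives (1.960 + 1.282)² × 6.057 / 0.92² = 75.2, so 76, and 76/0.9 gives 85. The Welch t calculation gives 77 (power 0.902), and 77/0.9 = 85.6, so 86. The article's 86 per arm is reproduced, with 77 evaluable.

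**4. How often a pathway is named.** The simulation used 77 per arm and 2000 runs per cell. Assumed, because the article gives no figures: 300 metabolites, one pathway of 20 members with correlation 0.5, and an arm contrast. The rule was a t-test per metabolite, BH-FDR < 0.05, then hypergeometric enrichment p < 0.05; the VIP filter was not simulated.

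| CJG shift in pathway metabolites | No nodule effect | 0.92 mm, pathway inert | 0.92 mm, all through pathway |
|---|---|---|---|
| 0 | 0.001 | 0.001 | not applicable |
| 0.3 SD | 0.17 | 0.17 | 0.17 |
| 0.5 SD | 0.76 | 0.75 | 0.73 |
| 0.8 SD | 1.00 | 1.00 | 1.00 |

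The metabolite data are generated identically across each row, so differences within a row are simulation noise.

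**5. With a link to the nodule added.** The rule was extended to require, in addition, an arm-adjusted association between the pathway score and nodule change (p < 0.05, robust standard error). In the same column order, the rates become:

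- 0.3 SD: 0.01 / 0.01 / 0.17
- 0.5 SD: 0.05 / 0.04 / 0.73
- 0.8 SD: 0.06 / 0.05 / 1.00

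The last column is a best case. At 0.3 SD, full mediation needs a slope of 0.92/0.3 = 3.07 mm per unit. With a within-arm score variance of 0.5, the pathway alone contributes 0.5 × 3.07² = 4.7 mm², more than the pilot variances of 4.49 and 1.56. At 0.5 SD it contributes 0.5 × 1.84² = 1.69, more than 1.56. The residual variance was then set to a small floor, which makes the link almost deterministic.

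A second simulation gives a more sober view of power. It used 400 metabolites in blocks of 20 with correlation 0.3, 400 runs, and a common SD of √(6.057/2) = 1.74 mm in the linked cases. An FDR screen by arm followed by an FDR-controlled partial correlation with ΔD had power 0.62, 0.79 and 0.93 at within-arm correlations of 0.25, 0.30 and 0.35. It flagged unlinked features in 0.03 to 0.06 of trials.

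**The case against.** The strongest reply is that the article claims less than this suggests. The section is headed exploratory, the quoted aim speaks of potential pathways, the output of KEGG is described as altered pathways, and the paragraph closes by calling the work hypothesis-generating. Whether CJG changes nodules at all is tested separately by the mixed model, so a null nodule result would be visible. A condensed article may also leave an omics-by-outcome analysis to a fuller plan.

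Most of this stands, and it keeps the point small. It does not remove the mismatch. The article names its steps, and it attaches the bridge to CT findings to one of them. That sentence is wrong about that step whatever a fuller plan adds. The mixed model covers the case of no nodule effect, but not a nodule effect that runs by another route.

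Two stronger readings are tempting, and the document does not support either. One is that the analysis would name a mechanism in nearly every trial whatever CJG does. Section 2.7.4 includes FDR control, and with no metabolite shift the simulated rule names the pathway in about 0.001 of trials; the equality across nodule states holds only for a given effect on metabolites. The other is that the trial will declare a proven causal mechanism. The hedges just listed rule that out.

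**Conclusion.** The stated steps can test whether CJG alters saliva or stool. They cannot test whether that alteration bears on the nodule, so they do not support the claims to move past correlation and to link CT findings with mechanism. For a fixed metabolite effect the naming rate is identical across nodule states: about 0.17, 0.75 and 1.00 at 0.3, 0.5 and 0.8 SD. The identity needs no assumption beyond the inputs listed in section 2.7.4. The rates themselves depend on the assumed number of metabolites, pathway size and correlation, on the omitted VIP filter, and on reading differential as between arms, which the article does not specify. This is a modest point about exploratory work; the primary, secondary and safety analyses and the sample size are unaffected.

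**What to change.** **Section 2.7.4.** For each genus or metabolite that differs between arms at FDR < 0.05, add a regression of month-3 ΔD on the feature's change from baseline, adjusted for arm, baseline diameter and age, with robust standard errors and BH-FDR over the features tested. Keep KEGG enrichment on all differential metabolites as a description of altered pathways. Call a pathway a candidate mechanism of nodule effect only if its features are also associated with ΔD.

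**Discussion.** Replace the phrase on moving beyond correlation to causal pathways, and the phrase on bridging to CT findings. Say instead that the steps show CJG-associated changes in saliva and stool, and that any association with ΔD is a hypothesis about mediation. If no regression is added, the narrower wording on saliva and stool alone would cure the mismatch.

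**Cost.** One further regression and some wording, on samples and CT scans already scheduled. This assumes that placebo participants are sampled on the same schedule, which section 2.7.4 does not say outright. Fewer features will be labelled mechanistic, and power for weak links is modest (about 0.62 at a within-arm correlation of 0.25). The simulated pathway-score version is close to the proposed per-feature version but not identical to it. The association would still not prove mediation, because the mediator is not randomised.
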